## Abstract

**Introduction:**

Fibromyalgia (FM) is a chronic condition characterized by widespread pain and cognitive dysfunction, with pharmacological treatments offering limited efficacy. Although Pain Neuroscience Education (PNE) and therapeutic exercise are evidence-based interventions, accessibility and adherence remain major challenges particularly in underserved regions such as Latin America. This trial investigates the effectiveness of a 12-week tele-rehabilitation program (FIBROIA) that integrates Artificial Intelligence (AI)-guided exercise with PNE to enhance access to comprehensive multimodal care.

**Methods and analysis:**

This multicentre, randomized, assessor-blinded, parallel-group controlled trial will enroll fifty adults meeting the 2016 ACR criteria for FM. Participants will be randomly assigned (1:1) to either the intervention group or enhanced usual care. The intervention consists of three personalized exercise sessions per week delivered through the Rehbody AI platform, which provides real-time biomechanical feedback, along with a weekly PNE module designed to reconceptualize pain. The primary outcome is the change in pain intensity, measured using the Visual Analogue Scale (VAS), at week 13 (±7 days), immediately following completion of the 12-week program. Secondary outcomes include the Fibromyalgia Impact Questionnaire–Revised (FIQ-R), lower-limb strength assessed by the 30-Second Sit-to-Stand test, and health-related quality of life measured with the EQ-5D-3L. Statistical analyses will follow an intention-to-treat (ITT) framework.

**Discussion:**

The FIBROIA protocol addresses the urgent need for scalable, evidence-based interventions in resource-limited settings. By combining AI-driven biomechanical feedback with cognitive reappraisal through PNE, this study seeks to reduce fear-avoidance behaviors and improve exercise adherence. This integrative approach aims to overcome the limitations of passive tele-rehabilitation by simulating asynchronous professional supervision, thereby ensuring both safety and technical precision in movement execution.

**Conclusions:**

If effective, this protocol will offer a robust, technology-enabled framework for remote FM management. The results could help establish a new clinical standard for accessible, patient-centered rehabilitation, bridging the gap between high-level evidence and real-world practice across diverse socioeconomic contexts.

**Trial registration:**

ClinicalTrials.gov NCT06672419.

## Introduction

Fibromyalgia (FM) is a chronic, complex, and disabling condition affecting approximately 2–4% of the global adult population [1]. It is characterized by widespread musculoskeletal pain, persistent fatigue, non-restorative sleep, cognitive dysfunction, and psychological comorbidities such as anxiety and depression, all contributing to substantial impairment in daily functioning and quality of life [2,3]. FM predominantly affects women, and recent epidemiological estimates suggest that more than 700,000 individuals in Latin America may be living with the condition, many of whom remain undiagnosed or receive suboptimal care [4].

The pathophysiology of FM is multifactorial, with central sensitization recognized as a principal underlying mechanism. This involves altered nociceptive signaling, impaired endogenous pain inhibition, neuroinflammatory processes, and dysfunctional cortical processing of sensory inputs [5,6]. Although pharmacological treatments such as tricyclic antidepressants, serotonin–norepinephrine reuptake inhibitors, anticonvulsants, and non-opioid analgesics are frequently prescribed, they typically yield only modest symptom relief and are often limited by adverse effects that compromise long-term adherence [7]. Consequently, current international guidelines recommend non-pharmacological interventions, including aerobic and resistance exercise and cognitive-behavioral strategies, as first-line therapies for FM [8,9].

Among these, Pain Neuroscience Education (PNE) has emerged as a promising approach that reconceptualizes pain within a biopsychosocial framework. PNE is an educational intervention designed to help individuals understand the neurophysiological and psychological mechanisms of pain, emphasizing central sensitization, neuroplasticity, and the interplay between cognitive, emotional, and perceptual processes. It aims to modify maladaptive beliefs such as catastrophizing and fear-avoidance while promoting active coping, behavioral engagement, and self-management [10,11]. Evidence from randomized controlled trials and systematic reviews supports the efficacy of PNE, particularly when combined with exercise, in reducing pain severity, enhancing physical function, and alleviating emotional distress among individuals with FM and other chronic pain conditions [12–15].

Telerehabilitation has emerged as a scalable and accessible modality for delivering rehabilitation interventions remotely via digital communication technologies. It encompasses synchronous (real-time video-based), asynchronous (app- or web-based), and hybrid models, thereby facilitating continuity of care and multidisciplinary collaboration beyond conventional clinical settings. Telerehabilitation has demonstrated benefits in improving adherence, engagement, and access to treatment for individuals who face geographical, logistical, or economic barriers to in-person care.

Recent advances in artificial intelligence (AI) and computer vision (CV) technologies have further expanded the potential of telerehabilitation by enabling automated motion tracking, remote supervision, and individualized progression of exercise programs. AI-driven algorithms can detect movement deviations, provide real-time corrective feedback, and adjust exercise intensity according to each participant’s functional capacity enhancing both safety and personalization. Although these technologies have shown promising outcomes in neurological and musculoskeletal rehabilitation, their application to fibromyalgia remains limited and underexplored [16–19].

Despite robust clinical evidence supporting non-pharmacological management, implementation across Latin American health systems continues to be hindered by workforce shortages, infrastructural limitations, geographical dispersion, and unequal access to specialized care [4]. In this context, integrating PNE with AI-assisted telerehabilitation represents an innovative, evidence-informed, and potentially scalable approach to improving FM management in resource-constrained settings.

The present study aims to evaluate the effectiveness of a 12-week telerehabilitation program integrating AI-guided exercise and PNE in reducing pain intensity and improving physical function and quality of life among adults with FM, compared with enhanced usual care. It is hypothesized that participants receiving the combined digital intervention will demonstrate significantly greater improvements in pain outcomes, functional performance, and biopsychosocial well-being than those receiving standard care.

## Methods and analysis

### Trial design and context

This study is a decentralized, assessor-blinded, parallel-group, randomized controlled trial designed to evaluate the effectiveness of a 12-week tele-rehabilitation program integrating artificial intelligence (AI)–guided exercise and Pain Neuroscience Education (PNE), compared with enhanced usual care, in adults with fibromyalgia (FM). Assessments will be conducted at baseline (Week 0) and post-intervention (Week 13 ± 7 days), immediately following completion of the 12-week program. The trial is prospectively registered at ClinicalTrials.gov (NCT06672419). Any protocol-relevant amendments (e.g., updates to masking descriptions or study setting terminology) will be reflected in the registry and documented in the final manuscript.

The trial is coordinated by Universidad San Sebastián, with international collaboration from Universidad Santiago de Cali for technical support and data management. As a fully remote study, all intervention procedures are delivered online, and participants complete the program in their own homes.

Recruitment will be conducted through clinician referral networks and community outreach across Latin America. Collaborating healthcare professionals from diverse clinical contexts (e.g., primary care and specialized pain or rheumatology services) will inform potentially eligible patients about the study and provide standardized recruitment materials. These healthcare facilities serve solely as referral sources; no study procedures are performed on site, and no identifiable patient information is shared with the research team without explicit participant consent. Interested individuals will contact the coordinating research team directly (or authorize contact) to complete eligibility screening and provide electronic informed consent.

To ensure procedural consistency, all participants will use the same digital platforms Rehbody.net and ProyectoFibroBrain.org featuring identical intervention protocols, user interfaces, and data-capture mechanisms. Study personnel (physiotherapists providing remote supervision and outcome assessors) will undergo centralized training prior to trial initiation, including review of a detailed operations manual, practical workshops, and competency certification. Inter-rater reliability will be established before participant enrollment and reassessed annually to maintain measurement consistency among assessors.

Trial conduct will be monitored centrally through scheduled coordination meetings, periodic review of digital activity logs, verification of protocol adherence, and corrective measures in the event of deviations. Outcomes will be collected via standardized procedures using validated Spanish-language instruments within the REDCap platform, ensuring harmonized data collection, coding, and secure transmission.

The trial will adhere to the SPIRIT 2013 statement [20] (including relevant updates aligned with SPIRIT 2025) and the CONSORT 2010 reporting standards [21,22] (see S1 Appendix).

### Patient and public involvement in trial design

During the planning phase, individuals with FM and representatives from patient support organizations across Latin America were consulted to capture their lived experiences, barriers to care, and perspectives on digital health interventions. Their contributions were instrumental in adapting the trial to patient needs.

A group of patients reviewed a preliminary version of the PNE manual, providing feedback that improved clarity, sequencing, and illustrative examples. Based on their input, comprehension questions were added to each module to reinforce learning. Patients also evaluated the usability of the AI-guided exercise component, leading to modifications in difficulty, pacing, and structure to enhance safety and personalization.

Concurrently, the PNE modules were reviewed by physiotherapists, clinical researchers, and pain science educators with expertise in the biopsychosocial model of chronic pain. This process ensured conceptual accuracy, pedagogical coherence, and cultural relevance. The final 12-module sequence was refined iteratively through patient and expert feedback, consistent with international standards for digital patient education [24,25,27].

Public involvement will continue throughout the trial via dissemination initiatives, including community webinars, open-access educational materials, and lay summaries. The final version of the PNE manual is publicly available online to promote equitable access to knowledge and support patient-centered learning.

### Eligibility criteria

Adults aged 18–65 years of any sex, with a confirmed clinical diagnosis of FM based on the 2016 American College of Rheumatology criteria [1], will be eligible. Participants must have reliable access to an internet-connected device (e.g., smartphone, tablet, or computer) and the ability to participate in a structured tele-rehabilitation program.

### Inclusion criteria

Clinical diagnosis of FM according to ACR 2016 criteria.Age between 18 and 65 years.Ability to understand and communicate in Spanish.Access to a stable internet connection and a device capable of supporting telehealth interactions.Willingness and ability to complete the 12-week program.Provision of informed consent.

### Exclusion criteria

Participation in another clinical trial within the past three months.Current pregnancy or breastfeeding.Presence of uncontrolled severe medical conditions (e.g., cardiac arrhythmias, severe pulmonary disease) that may limit participation.Physical disabilities or acute musculoskeletal injuries preventing execution of exercise routines (e.g., recent fractures, trauma).Severe cognitive impairment or neuropsychiatric disorder that hinders comprehension or adherence, defined as a score < 24 on the Mini-Mental State Examination, < 26 on the Montreal Cognitive Assessment, or equivalent validated screening tool.Severe uncorrected visual or auditory impairments interfering with digital interaction.

### Participant selection, recruitment, and consent

Participants will be identified through professional networks of the research team and outreach initiatives by collaborating centers in Latin America. Trained study personnel will verify eligibility using medical records and structured interviews.

Eligible individuals will be contacted via telephone or videoconference and provided with a digital information sheet describing study objectives, procedures, potential risks, and benefits. Informed consent approved by institutional ethics committees will be obtained electronically prior to baseline assessment or intervention initiation.

Following consent, participants will complete baseline demographic, clinical, and functional evaluations before randomization (Figs 1 and 2).

**Fig 1 pone.0349017.g001:**
[figure not shown]
Organization according to the checklist time and interventions.

**Fig 2 pone.0349017.g002:**
[figure not shown]
Study design. Participants (n = 50) will be randomized to either the intervention group (AI-guided tele-rehabilitation + PNE) or enhanced usual care. The intervention will last 12 weeks. Assessments will occur at baseline (Week 0) and immediately after program completion (Week 13 ± 7 days).

### Sample size

The sample size was calculated a priori to ensure both feasibility and statistical rigor. The calculation targeted the primary endpoint of pain intensity (VAS, 0–10 scale) from baseline to week 13. A minimal clinically important difference (MCID) of 2.0 cm and an expected standard deviation (SD) of 3.0 cm were assumed, based on previous randomized controlled trials in fibromyalgia populations evaluating pain reduction through behavioral and digital interventions [28,35]. Under these parameters, a total sample of 50 participants (25 per group) provides 80% power (two-tailed, α = 0.05) to detect a moderate-to-large effect size (Cohen’s d ≈ 0.65), using an independent t-test. The calculation was performed using G*Power software (version 3.1.9.6).

An attrition rate of approximately 10% was anticipated. Although higher dropout rates have been reported in some digital health trials, this estimate was considered reasonable given the structured follow-up, the short intervention period (13 weeks), and previous experience from our group showing high retention (>90%) in similar telehealth interventions for chronic pain. The sample size remains adequate after accounting for this expected loss. This calculation was finalised prior to recruitment to ensure prospective justification.

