### Randomisation and allocation concealment

Randomisation will be performed using a computer-generated sequence with a 1:1 allocation ratio, employing permuted blocks of variable size (4–8 participants) to reduce allocation predictability. To minimise selection bias, randomisation will be stratified by age (<50 vs ≥ 50 years), given the established influence of age on FM outcomes.

Allocation concealment will be maintained through a centralised, web-based system (REDCap, Vanderbilt University), operated by an independent researcher not involved in intervention delivery or outcome assessment. This system provides automatic participant assignment with timestamped allocation records, ensuring transparency and traceability.

If web-based randomisation is unavailable, a validated contingency procedure will be implemented using sequentially numbered, opaque, sealed envelopes (SNOSE) prepared off-site by an independent statistician. Envelopes will be tamper-proof, opaque, and opened sequentially only after participant enrolment and baseline assessment.

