### Data analysis

Analyses will follow both intention-to-treat (ITT) and per-protocol (PP) principles, consistent with CONSORT recommendations [21]. The ITT population will include all randomised participants, analysed according to their allocated group. Missing outcome data will be addressed using multiple imputation, assuming data are missing at random. Sensitivity analyses using last observation carried forward (LOCF) and complete-case approaches will be performed to assess the robustness of the findings.

The PP population will include participants who complete at least 80% of the prescribed intervention dose (≥29/36 exercise sessions and ≥10/12 PNE modules) and have no major protocol deviations. Baseline characteristics will be summarised descriptively and compared between groups using parametric (independent t-test) or non-parametric (Mann–Whitney U test) methods, depending on normality assessed via the Shapiro–Wilk test.

The primary analysis will evaluate the change in pain intensity (VAS, 0–10 cm) from baseline to week 13 (±7 days) between groups using both independent t-tests and Mann–Whitney U tests to ensure consistency of results. The anticipated effect size (Cohen’s d ≈ 0.65) was derived from prior trials of multidisciplinary and digital interventions in fibromyalgia, which reported moderate-to-large effects on pain reduction (range 0.5–0.7) [28,36,37]. Within-group changes will be assessed using paired t-tests or Wilcoxon signed-rank tests, as appropriate. Effect sizes (Cohen’s d) with 95% confidence intervals will be reported and interpreted using conventional thresholds [38].

Secondary outcomes (FIQ-R, 30-Second Sit-to-Stand, EQ-5D, NRS-Anxiety, adherence barriers) will be analysed using similar methods. Minimal clinically important differences (MCIDs) will be defined a priori as follows: 14% for FIQ-R total score, ≥ 2 repetitions for the 30-Second Sit-to-Stand, and ≥0.07 for EQ-5D index, based on previous validation studies. For repeated measures, mixed-effects models will account for within-subject correlations and time effects [39,40]. Multivariable regression analyses will adjust for relevant covariates (e.g., baseline pain, age, pharmacological treatment).

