Pre-specified subgroup analyses will explore treatment effects according to baseline pain severity (VAS ≥ 7 vs. < 7), age group (<50 vs. ≥ 50 years), and pharmacological treatment status (yes/no). Secondary outcomes will be considered exploratory. No formal multiplicity adjustment will be applied; effect estimates will be reported with 95% confidence intervals to support interpretation

All statistical tests will be two-tailed with α = 0.05. Analyses will be performed using IBM SPSS Statistics v28.0 and R software v4.3.2. Results will be presented with effect sizes, confidence intervals, and graphical summaries.

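### The sample size statement claims 80% power, but its own inputs give about 62–64% with 25 per group, and about 57–59% after the anticipated 10% loss

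*Protocol article*

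**What the plan says.** The Sample size section sets out every input of the calculation. On the effect: "A minimal clinically important difference (MCID) of 2.0 cm and an expected standard deviation (SD) of 3.0 cm were assumed". On the result, it says that "a total sample of 50 participants (25 per group) provides 80% power". The test behind this figure is a two-sided independent t-test at the 5% level, and the standardised effect is given as about 0.65. The section names G*Power as the software and describes the calculation as made before recruitment.

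The same section anticipates about 10% attrition and concludes: "The sample size remains adequate after accounting for this expected loss".

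Other sections agree with these inputs. The randomisation section specifies a "computer-generated sequence with a 1:1 allocation ratio". The Data analysis section names the independent t-test on change in VAS, alongside a Mann–Whitney U test, as the primary analysis. It repeats d ≈ 0.65 and places it within a range of 0.5–0.7 taken from earlier trials, "which reported moderate-to-large effects on pain reduction". It also confirms the error rate: "All statistical tests will be two-tailed with α = 0.05". The abstract and the study design figure legend both give 50 as the number enrolled or randomised.

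**The concern.** A standardised effect near two thirds is well known to need more than 25 per group for 80% power in a two-sided two-sample t-test, so the stated figure looked too high on sight. The attrition sentence raises a second doubt. The 50 participants said to give 80% power are the same 50 to be randomised, so any loss must take power below whatever 50 provides.

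The stake is the operating characteristic that the trial reports for its only primary endpoint. A reader who accepts 80% power may take a non-significant result as fairly strong evidence against a 2.0 cm benefit. At the real power that inference is much weaker. The Strengths and limitations section mentions the small sample only as a limit on generalisability, so it does not disclose the shortfall.

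**Working it through.** **Inputs, all from the protocol article**
- Difference 2.0 cm, SD 3.0 cm, d quoted as about 0.65 (Sample size). The exact ratio is 2.0/3.0 = 0.667, so both values are carried.
- Two-sided α = 0.05 (Sample size; Data analysis).
- Independent t-test, 25 per group, 1:1 (Sample size; Randomisation).
- Attrition 10%: 50 × 0.9 = 45 evaluable, split 23/22.

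**Step 1. Try to reproduce the stated 80%.**
For a two-sample t-test the noncentrality is δ = d·√(n₁n₂/(n₁+n₂)), with n₁+n₂−2 degrees of freedom. Power is the probability that a noncentral t variable falls beyond the two-sided 5% critical values.

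With 25/25, √(625/50) = 3.536:
- d = 0.667: δ = 2.357, power **63.7%**
- d = 0.65: δ = 2.298, power **61.5%**

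Hand check by the normal approximation, Φ(δ − 1.96): Φ(0.397) = 65.4% and Φ(0.338) = 63.2%. The 80% is not reproduced.

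**Step 2. Apply the plan's own attrition.**
With 23/22, √(506/45) = 3.353:
- d = 0.667: δ = 2.236, power **58.9%**
- d = 0.65: δ = 2.180, power **56.8%**

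**Step 3. Look for a reading that gives 80% with 25 per group.**

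| Variant | Power |
|---|---|
| One-sided α = 0.05, d = 0.65 / 0.667 | 73.3% / 75.1% |
| Mann–Whitney, relative efficiency 0.955, d = 0.65 / 0.667 | 59.4% / 61.6% |
| Two-sided t-test, d = 0.5 (bottom of the quoted range) | 41.0% |
| Two-sided t-test, d = 0.7 (top of the quoted range) | 67.9% |
| Paired or one-sample t-test, n = 25, d = 0.65 / 0.667 | 87.6% / 89.2% |

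None gives 80%. The paired test overshoots and is not the between-group comparison that the plan describes.

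**Step 4. What 50 randomised can detect with 80% power.**
- 25/25: d = 0.809, and 0.809 × 3.0 = 2.43 cm
- 23/22: d = 0.855, and 0.855 × 3.0 = 2.56 cm

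**Step 5. What 80% power needs at the stated effect.**
- d = 0.667: 37 per group, 74 evaluable; 74/0.9 = 82.2, so 83 randomised, or 84 in equal groups
- d = 0.65: 39 per group, 78 evaluable; 78/0.9 = 86.7, so 87 randomised, or 88 in equal groups

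**Step 6. Expected precision at SD 3.0 cm.**
The 95% CI half-width is t₀.₉₇₅ × 3.0 × √(1/n₁+1/n₂).
- 25/25: 2.011 × 0.849 = 1.71 cm
- 23/22: 2.017 × 0.895 = 1.80 cm

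Both are close to the 2.0 cm that the plan calls the MCID.

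**The case against.** The best defence is that the Data analysis section also plans regression adjusted for baseline pain, and mixed models, which can be more efficient than an unadjusted t-test. If 3.0 cm is the SD of the raw week-13 score and the correlation between baseline and week 13 is about 0.6, an adjusted analysis with 25 per group would have 80.4% power (d = 0.65) or 82.3% (d = 0.667). So 62–64% is the power of the named test, not a ceiling for every planned analysis. But the protocol states no correlation, bases the calculation on an independent t-test and names unadjusted tests of change as primary. Even with that correlation, power falls below 80% after attrition: 75–77% with 22 per group.

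A second objection is that multiple imputation keeps all randomised participants in the analysis, whereas the 57–59% counts the missing 10% as carrying no information. That is a simplification. With only a baseline and one later assessment, imputation would recover little, and it cannot restore power that is absent at full enrolment.

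Third, the plan already commits to effect sizes with 95% confidence intervals, which gives some protection against over-reading a null result. That is fair: over-reading is a risk, not a certainty. Finally, the 0.5–0.7 range in the Data analysis section is not itself an error. It matters here only because no value in it reaches 80% with 25 per group.

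**Conclusion.** The concern holds. The document fixes every input, and the stated power does not follow from them. It is 61.5–63.7% instead of 80%, a shortfall of 16.3 to 18.5 percentage points. With 45 evaluable it is 56.8–58.9%, a shortfall of 21 to 23 points. Rounding d from 0.667 to 0.65 accounts for only about 2 points. The claim of adequacy after attrition fails as well, and would fail even if 50 gave exactly 80%, because nothing was added for loss.

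These figures assume that 3.0 cm is the SD of the variable tested, that the two-sample t-test is the primary test as written, and that lost participants add no information. This is a wrong numerical statement about the primary endpoint, not a detail left to an analysis plan, and it must be corrected.

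**What to change.** Correct the Sample size section as follows.

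1. Replace the power sentence with one along these lines: *Fifty randomised participants (25 per group) give 64% power for a 2.0 cm difference at SD 3.0 cm (two-sided α = 0.05, independent t-test), or 59% with 45 evaluable. Power of 80% is reached for a difference of about 2.4 cm, or 2.6 cm with 45 evaluable.* Use d = 0.667 throughout, or explain why 0.65 is used and quote 62% and 57%.
2. Delete the sentence saying that the size stays adequate after the expected loss.
3. State that a non-significant primary result will be read from the 95% CI (expected half-width about 1.7–1.8 cm) and not as absence of effect.
4. If a baseline-adjusted analysis is made primary, quote its power with the assumed baseline correlation and say which SD the 3.0 cm refers to.

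This costs wording and a less favourable power figure; no extra participants are needed. If the sponsor wants to keep the 80% claim for 2.0 cm, the alternative is to enlarge the trial to about 84–88 randomised, which is 34–38 more than planned. The ethics section says that nobody had been recruited at submission, so that choice was still open then.
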